## Intervention

### Physical exercise program at home

The home exercise program will be based on the recommendations of the American College of Sports Medicine for exercise and physical activity of elderly people [3]. The program consists of aerobic exercises, muscle strengthening exercises, balance training, motor coordination, and flexibility, always prioritizing exercises involving large muscle groups. The protocol will last for 12 consecutive weeks, with a minimum frequency of three sessions per week and a planned execution time of 40 min. During each session, two to three sets will be performed with 5 to 15 repetitions for each exercise at a target effort rate of 13–15 (“a little difficult” to “difficult”) on Borg’s perceived exertion scale of 6 to 20 points [20].

The participant will perform the exercise program individually in their own home, without direct supervision during its execution, but with on-site guidance through home visits every 15 days by one of the members of the team. Participants will be instructed to increase the intensity of the exercises, using the Borg scale to evaluate intensity, and in a manner proportional to their execution capacity, evaluated by the research assistants at each of the visits. The exercises will be carried out using the weight of the body itself and with the aid of some low-cost equipment (recyclable plastic bottles to demarcate the signage of the course, sticks and weights of 1 and 2 kg for performing the resistance exercises). The following are the exercises to be performed:Warm-up exercises – Active-free exercises of the upper and lower limbs, including extension, flexion, and rotation of the shoulders associated with breathing exercisesAerobic exercises – Displacement of a stick with both hands, from the knees to above the head and returning to the knees, and walking exercises with alternating thigh flexion and placing the hand on the opposite kneeResistance exercises – For the upper limbs: starting from the position with the elbow extended and the hand resting on the opposite thigh, movement of the whole member diagonally upwards and then returning the hand to the thigh. For the lower limbs: squatting exercise, starting from the sitting position on a chair and with arms crossed in front of the body, lifting to the orthostatic position and then returning to the sitting positionBalance and coordination exercises – Walking on a straight line and walking while diverting from lined obstacles with progressively smaller distances. When possible, the exercise will evolve and the walk will be performed by touching the heel of one foot to the toes of the other foot (foot with foot)Note: to ensure safety, these exercises will be performed close to fixed furniture in the house, making it possible to lean when necessaryStretching exercises – From the sitting position and with knees in extension, trying to reach the tip of the feet; from the sitting position on a chair and with the feet on the ground, performing rotation of the trunk to one side and elevation of the upper limb, on the same side, above the head, stretching as high as possible

During the period of the proposed program (12 consecutive weeks), regular home visits will be made to the participants of the two groups in order to clarify doubts, guide healthy living habits, and encourage adherence to the program. The IG will receive, in addition to these guidelines, specific monitoring in relation to the practice of the exercises and assistance with possible adverse events. After the end of the proposed 12-week period, the researchers will reassess the participants in both groups and encourage them to continue with the home program. Those in the CG will be provided follow-up for the regular practice of home exercises for the same period performed by the IG participants.

### Statistical analysis

The principle of intention-to-treat analysis will be respected. For missing data, we will perform a sensitivity analysis, through simple imputation, using the mean of the variables. Student’s *t* test for numerical variables and Pearson’s chi-square test for categorical variables will be applied to verify whether the randomization process generated two groups of subjects (CG and IC) with homogeneous clinical and demographic characteristics before intervention, thus avoiding a possible selection bias. To test the normality of the data, an analysis of the study histogram, mean and median, standard deviation, skewness, and kurtosis will be performed and for its confirmation, we will use the Shapiro-Wilk normality test. With a normal distribution of variables, parametric statistics will be used, and intragroup comparisons will be made using the Student’s *t* test for paired samples; the intergroup comparisons will be performed using the Student’s *t* test for independent samples. If there is no normal distribution of the variables, the corresponding non-parametric tests will be used. For the analysis of the groups by age, as will be done with more than two groups, we will use the one-way analysis of variance (ANOVA) for parametric distribution or Kruskal-Wallis for non-parametric analysis. The significance level established for all analyses will be *p* < 0.05 and all statistical procedures will be analyzed and processed using the Statistical Package of the Social Sciences SPSS 21.0 software (IBM® SPSS version 21, IBM, Armonk, NY, USA).

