## Methods/design

### Study design and setting

The design and conduct of this study follows the guidelines of The Standard Protocol Items “Recommendations for Intervention Trials (SPIRIT) guidelines” [13], according to the flow chart of the study showed in Fig. 1. This is a blind, randomized controlled clinical trial, using a superiority test and a 1:1 allocation ratio. The sample will be of convenience, composed of elderly subjects in a community in the city of Senhor do Bonfim, BA, northeastern region of Brazil. The protocol is reported according to the Standard Protocol Items: Recommendations for Interventional Trials (Fig. 2 SPIRIT diagram and Additional file 1: SPIRIT Checklist).

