### Sample size

The sample size was calculated using the WINPEPI (PEPI-for-Windows) [21] software, based on the main hypothesis of the study. According to a relevant study published by Lacroix et al. [8], where a group of health older adult subjects performed unsupervised exercises obtaining a reduction of 0.37 s in TUG execution time when compared to pre and post intervention with duration of 12 weeks. Considering the standard deviation of 0.84 for the IG and 1.02 for the CG observed in the study, with a statistical power of 80% and an alpha error of 5%, 101 participants in each group would be necessary. The sample will be increased by 10% to compensate for possible dropouts, leading to 111 subjects in each group (overall sample = 222 participants).

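### The only stated missing-data method is single mean imputation, with the type of mean left open; neither the arm mean nor the overall mean gives a sound robustness check

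*Protocol article*

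**What the plan says.** The Statistical analysis section of the protocol article opens with a commitment: "The principle of intention-to-treat analysis will be respected". The next sentence is its only statement on missing values: "For missing data, we will perform a sensitivity analysis, through simple imputation, using the mean of the variables". Whether the mean is taken within each arm or over both arms is not stated. The between-arm test is then given: "the intergroup comparisons will be performed using the Student’s *t* test for independent samples", with a non-parametric counterpart if normality fails.

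Missing outcomes are expected. The Sample size section says "The sample will be increased by 10% to compensate for possible dropouts", which takes 101 per group to 111. The section on retention adds that a participant who leaves is to be replaced. That is a recruitment rule, and it does not supply the outcome of the randomised person who left.

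The Primary outcome section defines the endpoint as the change in TUG between baseline and 3 months. It does not say whether imputation is applied to the change itself or to the 3-month value from which the change is computed.

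**The concern.** A sensitivity analysis for missing data should show whether the conclusion survives other plausible assumptions about the unseen values, with honest uncertainty around the result. Single mean imputation enters each filled-in value as if it had been observed, so the t test counts people who contributed no outcome as full information.

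The consequence depends on which mean is used. With arm means, the standard error is too small and the check tends to endorse a positive result too readily. With the overall mean, the between-arm difference is pulled towards zero by an amount fixed by the missing fraction. Either way, agreement or disagreement with the main result would partly be an artefact of the method. The article names this method, so the point concerns a stated choice and not a detail left to an analysis plan.

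**Working it through.** **Inputs.** From Sample size: difference 0.37 s ("obtaining a reduction of 0.37 s in TUG execution time"); SDs 0.84 and 1.02 ("Considering the standard deviation of 0.84 for the IG and 1.02 for the CG observed in the study"); power 80%, alpha 5%; 111 randomised per arm; 10% loss. From Study design and setting: 1:1 allocation. Assumed here: equal and completely random loss in both arms, and a loss of 20% as a second case.

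**The plan's own figure.** SD = √[(0.84² + 1.02²)/2] = 0.934. n = 2 × [0.934 × (1.960 + 0.842)/0.37]² = 100.1, so 101 per group. This matches the stated figure with a two-sided test. 101 × 1.10 = 111.1, stated as 111.

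With N = 111 randomised and loss d = 10%, about m = 100 are observed per arm. At 20%, m = 89.

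**A. Arm mean, analysed outcome imputed directly.** The estimate equals the complete-case estimate.
- True SE = 0.934 × √(2/100) = 0.132.
- SE the t test reports = 0.934 × √(99/110) × √(2/111) = 0.119.
- Ratio = 0.90, in general about 1 − d.
- Type I error = 2 × P(Z > 1.96 × 0.9005) = 7.8%, so a nominal 95% interval covers about 92.2%. Simulation (40,000 runs) gave 7.7%.
- At 20%: ratio 0.801, type I error 11.6% (simulated 11.4%).

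**B. Arm mean, 3-month TUG imputed, change then computed.** Let baseline and 3-month TUG have equal variance σ² and correlation ρ. Per arm:
- True variance of the mean change = (σ²/N) × [2(1 − ρ) + d/(1 − d)].
- Variance the t test uses = (σ²/N) × [(1 − d) × 2(1 − ρ) + d].
- Their ratio is exactly 1 − d whatever ρ is, so the SE ratio is √(1 − d).
- At 10%: 2 × P(Z > 1.96 × 0.949) = 6.3%. At 20%: 2 × P(Z > 1.96 × 0.894) = 8.0%. Simulation gave 6.1–6.3% and 7.8–7.9%.

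**C. Overall mean.** Each arm mean becomes (1 − d) × the observed mean + d × the common mean, so the expected difference is multiplied by 1 − d. This holds for direct imputation and for change computed afterwards.
- At 10%: 0.37 × 0.90 = 0.333 s. At 20%: 0.37 × 0.80 = 0.296 s.
- Type I error stays near nominal: 4.9% simulated at 10% under direct imputation, and 4.9–5.1% when change is computed afterwards.
- Under direct imputation the reported SE also falls by about 1 − d, to 0.119. The test statistic hardly moves: 0.333/0.119 = 2.80 against 0.37/0.132 = 2.80 in complete cases. Simulated power is 79.5% against 79.4%. The estimate shifts, but the p-value is close to a copy of the complete-case one.

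**The case against.** The strongest case against the point has four parts.

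- **Literal wording.** The text speaks of the mean of the variables and does not mention arms, so one overall mean per variable is the more literal reading. Type I error is then about 5%. This stands: a reader might infer that the method gives a wrong error rate whichever mean is used, but the inflation belongs to the arm-mean reading only.
- **The overall mean does depart from the complete-case assumption.** At a true difference of 0.37 s it places dropouts about 0.185 s from the completers of their own arm, slower in the intervention arm and faster in the control arm. That is a crude move in the conservative direction, and it is conceded. It is a single fixed departure, however, and with direct imputation the reported SE shrinks with the estimate, so the test result is barely challenged.
- **Change scores.** A reader might infer that mean imputation never uses the missing person's baseline, always reproduces the complete-case estimate and always reduces the variance. If the 3-month TUG is imputed first, none of these holds. The person's own baseline enters the change, and at 10% loss the change-score variance is 0.9 + 0.1/[2(1 − ρ)] times the complete-case variance: 1.00, 1.07 and 1.40 at assumed ρ of 0.5, 0.7 and 0.9. The inflation is then smaller, but 6.3% is still above 5%.
- **It is only a sensitivity analysis.** A reader might infer that the trial's main test has an inflated error rate. The document does not support that: it attaches imputation to a sensitivity analysis and does not say that the imputed result replaces the main t test.

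**Conclusion.** The concern holds as a defect of the sensitivity analysis, on every reading of the sentence but with a different harm on each. At the planned 10% loss it is moderate: a type I error of about 7.8% or 6.3% with arm means, depending on what is imputed, or an expected effect of about 0.333 s in place of 0.37 s with the overall mean. At an assumed 20% loss the figures are about 11.6%, 8.0% and 0.296 s.

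All figures assume equal, completely random loss, and only the 10% rate comes from the document. The 6.3% and 8.0% figures also assume equal TUG variance at baseline and 3 months. The validity of the main between-arm test is not in question here. The change should be made, but the trial's main conclusion does not hang on it.

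**What to change.** Replace the sentence on mean imputation with two elements.

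1. Multiple imputation of the missing 3-month TUG, done separately within each arm, from variables the protocol already collects: baseline TUG, age, sex, and baseline WHOQOL-OLD and CHAMPS. Combine the results with Rubin's rules, so that uncertainty about the imputed values enters the standard error.
2. A shift analysis that makes the imputed intervention-arm TUG progressively worse, for example in steps up to the planned 0.37 s, and reports where the conclusion changes, if it does.

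A full 0.37 s shift at 10% loss moves the expected difference by 0.1 × 0.37 = 0.037 s, to 0.333 s, the same point that the overall mean reaches. The gain lies in the standard error: at about the complete-case 0.132 s the test statistic would be 0.333/0.132 = 2.52, not 2.80, so the result is actually put under strain. The 0.37 s limit is an example that the team may widen.

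The cost is some extra programming and a slightly wider interval. No new data and no change of sample size are needed.

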### Outcome measures

#### Primary outcome

The expected primary outcome is the change in the functional mobility of the elderly involved in the study, verified through the mean time in minutes for the TUG test, compared at the baseline and after the 3 months’ post-intervention period.

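### The analysis section names no single primary between-arm analysis and never adjusts for baseline TUG; the planned t test is valid, but one prespecified ANCOVA would be at least as precise and would settle the contrast

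*Protocol article*

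**What the plan says.** All references are to the protocol article.

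- **Between arms** (Statistical analysis): "the intergroup comparisons will be performed using the Student’s *t* test for independent samples". No covariate is named, and the text does not say whether the variable is the 3-month value or the change.
- **Within arms** (same section): "intragroup comparisons will be made using the Student’s *t* test for paired samples". One significance level, p < 0.05, is set for all analyses.
- **Switch of test** (same section): "If there is no normal distribution of the variables, the corresponding non-parametric tests will be used". Normality is judged from histograms and summary statistics and confirmed by Shapiro-Wilk.
- **Baseline tests** (same section): t and chi-square tests at baseline are meant to show that randomisation gave similar groups, "thus avoiding a possible selection bias".
- **Primary outcome**: change in functional mobility by TUG, "compared at the baseline and after the 3 months".
- **Sample size**: the effect comes from a study of unsupervised exercise "obtaining a reduction of 0.37 s in TUG execution time when compared to pre and post intervention". The spread is given as "Considering the standard deviation of 0.84 for the IG and 1.02 for the CG observed in the study", without saying whether these are SDs of a TUG time or of its change.

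TUG is measured before and after the intervention (Clinical evaluation), and allocation is prepared after the baseline assessment (Randomization and allocation concealment). Apart from forming the change, the only stated use of baseline values is the balance testing.

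**The concern.** Three things are left open or fixed poorly.

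1. **No named primary contrast.** The primary outcome is worded as a before/after comparison, the planning effect is a before/after reduction, and the analysis section lists paired and independent tests side by side at one significance level. A later report could rest on a significant change in the intervention group (IG) and a non-significant one in the control group (CG). That is not a test of the treatment effect. Equal improvement is plausible here, because both arms receive healthy-habit advice and regular home visits.
2. **Baseline TUG is not used as a covariate.** Available precision is left unused. If final values are compared, a chance baseline difference also stays in the estimate.
3. **The data choose the test.** Whether the result is a difference in means or a rank comparison is known only after the distribution has been examined.

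The rationale for the baseline tests is also wrong. Under proper randomisation any baseline difference is due to chance, and testing it neither prevents nor corrects selection bias.

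**Working it through.** **Inputs.** From Sample size: difference 0.37 s, SDs 0.84 (IG) and 1.02 (CG), power 80%, alpha 5% (two-sided reproduces the plan's figure; one-sided gives 79), 101 per arm before dropout. Assumed, because the article does not give it: correlation r between baseline and 12-week TUG, with equal variance at both times.

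**1. The plan's own figure.** Root mean square SD = √((0.84² + 1.02²)/2) = 0.934. n per arm = (0.84² + 1.02²)(1.960 + 0.842)²/0.37² = 100.1, rounded up to 101. With 101 per arm the noncentrality is 0.37/(0.934 × √(2/101)) = 2.81, and power is 80.0% (noncentral t). The stated number reproduces.

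**2. Effect of adjusting for baseline.** ANCOVA residual variance relative to a t test on final values is 1 − r². Relative to a t test on change it is (1 − r²)/(2(1 − r)) = (1 + r)/2. Neither ratio exceeds 1. Power for 0.37 s at 101 per arm:

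| Assumed r | Residual SD if 0.934 is of a single time: 0.934√(1 − r²) | Power | Residual SD if 0.934 is of change: 0.934√((1 + r)/2) | Power |
|---|---|---|---|---|
| 0.5 | 0.809 | 90% | 0.809 | 90% |
| 0.7 | 0.667 | 97.5% | 0.861 | 86% |
| 0.8 | 0.561 | 99.7% | 0.886 | 84% |

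The comparator is 80% in each column: the t test on the quantity that the SDs describe. The gain rises with r on the first reading and falls with r on the second.

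**3. Chance imbalance, if final values are compared.** Given a baseline difference of 2 standard errors and no treatment effect, the test statistic has mean 2r and variance 1 − r². The chance of |z| > 1.96 is then 0.13, 0.22 and 0.27 at r = 0.5, 0.7 and 0.8.

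**4. Within-arm tests.** Assume both arms truly improve by the same amount, SD of TUG 0.93 and r = 0.7, so the SD of change is 0.93√(2 × 0.3) = 0.72, with n = 101 per arm. Let p be the power of one paired test. Exactly one arm is significant with probability 2p(1 − p), and half of that is IG alone.

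| Common improvement (s) | p | Exactly one arm significant | IG alone |
|---|---|---|---|
| 0.05 | 0.106 | 19% | 9.5% |
| 0.10 | 0.282 | 40% | 20% |
| 0.15 | 0.545 | 50% | 25% |
| 0.20 | 0.789 | 33% | 17% |
| 0.25 | 0.932 | 13% | 6% |
| 0.30 | 0.986 | 3% | 1.4% |

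2p(1 − p) cannot exceed 50%, so the row at 0.15 s is the worst case. The between-arm test keeps its 5% error rate throughout.

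**5. The normality switch.** For lognormal TUG times (assumed), Shapiro-Wilk at 5% rejects in about 19%, 59% and just under 90% of simulated samples of 111 at a coefficient of variation (CV) of 0.10, 0.20 and 0.30 (4,000 samples each). In 3,000 simulated null trials with 101 per arm, the two-stage procedure on final values had type I error 0.058 at CV 0.15 and 0.051 at CV 0.30. The t test alone had 0.053 and 0.052.

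**The case against.** The strongest reply is that nothing planned is invalid. An unadjusted t test is a sound analysis of a randomised trial, the sample size was computed for exactly that test, and the trial has its stated power. The design section specifies a superiority test, and the Discussion frames the effect against a control population, so the randomised comparison is planned. All of this stands, and it limits the point to precision, chance imbalance and clarity about the primary contrast.

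Several stronger readings are tempting, but the article does not support them:

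- *The between-arm test ignores baseline.* The primary outcome is a change, so the t test may be on change, which uses baseline in part. That detail may be in a fuller plan. The article does fix the type of test, and neither version is adjusted.
- *Power would rise from 80% to nearly 100%.* That needs the planning SDs to be of a single TUG time and r to be high. If they are of change, the gain is 4 to 10 points at r from 0.8 down to 0.5.
- *The paired tests are the primary analysis.* They are listed separately and never called primary. The misreading is a risk left open, and its size depends strongly on the assumed common improvement.
- *The switch inflates error.* The simulations show type I error near 5%. Its frequency also depends on the assumed CV. The article gives no mean TUG, and with an SD of 0.93 a CV of 0.10 implies 9.3 s while 0.20 implies 4.65 s. Change scores would trigger it less often.
- *A rank test gives nothing in seconds.* A Hodges-Lehmann shift is in seconds, but it is a different estimand from the mean difference used for sizing.

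**Conclusion.** The point holds as an improvement that should be made; it does not show a biased or underpowered trial. The article fixes an unadjusted between-arm t test, gives within-arm tests the same significance level, lets a normality check decide the final test, and names no single primary analysis.

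Baseline adjustment would lift power at 101 per arm from 80% to between 84% and 99.7% over r = 0.5 to 0.8, depending on r and on which quantity the planning SDs describe. The efficiency result is asymptotic and the figures assume equal variances at the two times. Reading the within-arm tests as evidence of effect would mislead in a share of trials that varies from small to substantial: IG alone significant in about 1% to 25% under equal true improvement of 0.05 to 0.30 s. The switch costs a settled test and estimand, with little or no cost in error rate. The claim that baseline significance tests avoid selection bias is wrong whatever is assumed.

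**What to change.** In Statistical analysis, name one primary analysis: linear regression (ANCOVA) of 12-week TUG in seconds on randomised group and baseline TUG, reported as the adjusted mean difference with 95% confidence interval and robust standard errors. State that this model is kept whatever Shapiro-Wilk shows, with a rank-based analysis as sensitivity only. Use the same model for WHOQOL-OLD and CHAMPS. Report within-arm changes descriptively, without p values. Delete the statement that baseline significance tests avoid selection bias, and preferably the tests too, leaving a descriptive baseline table. Reword the primary outcome as a difference between arms at 12 weeks, and say whether the planning SDs are of TUG times or of changes.

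The cost is wording only: no new measurements, visits or participants, and 101 per arm remains adequate. Trial status says recruitment is still under way, so the change can be prespecified before outcome data are analysed by arm.
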